## Abstract

Back pain is one of the most costly disorders among the worldwide working population. Within that population, healthcare workers are at a high risk of back pain. Though they often demonstrate awkward postures and impaired balance in comparison with healthy workers, there is no clear relationship between compensatory postural responses to unpredictable stimuli and the strength of related muscle groups, in particular in individuals with mild to moderate back pain. This paper presents a study protocol that aims to evaluate the relationship between peak anterior to peak posterior displacements of the center of pressure (CoP) and corresponding time from peak anterior to peak posterior displacements of the CoP after sudden external perturbations and peak force during a maximum voluntary isometric contraction of the back and hamstring muscles in physiotherapists with non-specific back pain in its early stages. Participants will complete the Oswestry Disability Questionnaire. Those that rate their back pain on the 0–10 Low Back Pain Scale in the ranges 1–3 (mild pain) and 4–6 (moderate pain) will be considered. They will undergo a perturbation-based balance test and a test of the maximal isometric strength of back muscles and hip extensors. We assume that by adding tests of reactive balance and strength of related muscle groups in the functional testing of physiotherapists, we would be able to identify back problems earlier and more efficiently and therefore address them well before chronic back disorders occur.

## 1. Introduction

In 2019, the WHO reported that among musculoskeletal conditions, low back pain (LBP) is the leading cause of disability worldwide. In particular, work-related back pain is a major cause of reduced productivity and increased disability of workers, which places a significant financial burden on healthcare systems. Of all the professions, healthcare workers are at the highest risk of back problems [1,2,3,4,5,6,7,8,9,10]. This is due to overexertion of the back while handling patients, which may lead to awkward spinal postures and impaired static and dynamic balance.

Poor balance in itself may contribute to more severe back pain. Indeed, most LBP patients demonstrate impaired postural stability. For instance, differences exist in postural control strategy, the CoP displacement, and muscle activation patterns between people with and without non-specific LBP [11]. A greater postural instability, denoted by higher CoP velocity and excursions, has been found in people with non-specific LBP compared to healthy controls [12]. Their impaired postural stability seems to be associated with the presence of pain, whereas it is not related to the exact location and pain duration. There is no relationship between the magnitude of CoP excursions and the pain intensity.

Therefore, there is a need to identify more appropriate variables associated with back pain and to specify test conditions tailored to the requirements for assessment of healthcare workers with non-specific back pain in its early stages. Both the CoP and center of mass (CoM) variables should be measured in dynamic conditions with higher task demands. Standing on a spring-supported platform or a foam surface during testing is more efficient in identifying within- and between-group differences when compared to tests of static balance [13]. A good discriminatory accuracy in differentiating between sedentary and physically active young adults was also reported during a perturbation-based balance tests [14]. On the other hand, there were no significant differences in the magnitudes of CoP and CoM displacements in the mediolateral direction during unexpected surface translation in individuals with chronic LBP and healthy controls [15]. However, those with chronic LBP showed an earlier peak CoM displacement and later onset of initial CoP displacement [15]. Nonetheless, readjustment of postural stability in the anteroposterior direction after perturbations elicited by weight unloading has yet to be investigated.

The lumbar extensors and hip musculature may be an important factor in determining the motor control dysfunctions, such as limited balance, that arise in chronic LBP [16]. Lumbar extension strength has been shown to correlated significantly with Star Excursion Balance Test scores and explained ~19.3% to ~37.8% of its variance in the chronic LBP group and ~9.5% to ~16.9% in the asymptomatic group [16].

Traditionally, good isometric endurance of back muscles was sought to prevent first-time LBP occurrence [17]. The Sørensen test has been frequently used [18]. Such a measurement has been recommended as a standard for lifting tasks [19]. This was based on evidence that lower isometric strength is associated with LBP. However, the risk of back problems increases threefold when the requirements for lifting tasks are beyond or equal to their strength capacity. Static strength measurements underestimate the loads on the spine under dynamic conditions. The predicted spinal loads are 33–60% less under static than dynamic conditions depending on the lifting technique [20]. The recruitment patterns of trunk muscles and thus the internal loading of the spine are also different under these two conditions. Therefore, tests performed under dynamic conditions seem to be more appropriate for healthy as well as LBP populations. An exercise in the form of a deadlift to high pull that involves the major muscle groups in the lower and upper body may be able to simulate lifting tasks [21]. In such a case, a predictor of lifting performance with light loads might be a peak rate of force development (RFD) produced during a maximum voluntary isometric contraction (MVC) of the back muscles [22]. Thus, besides MVC peak force generated by back muscles, the subjects’ ability to produce a maximum force in a short period of time should by determined to obtain further insight into the loaded lifting performance in those prone to LBP.

In comparison with these frequently used strength and endurance tests of back muscles, less attention has been paid to the assessment of hamstring strength in LBP individuals and the associations with variables of postural and core stability measured in more challenging conditions. Though there is the belief that an association exists between a stronger body core and shorter reaction time, or stronger lower limbs and faster recovery, there is also an opposite view that suggests that stronger lower limbs contribute to slower recovery [23]. Therefore, a question remains as to whether reactive balance control after unpredictable stimuli is associated with the strength of relevant muscle groups in the high-risk population of healthcare workers.

This paper presents a protocol for a cross-sectional study that will investigate the relationship between peak anterior to peak posterior displacements of the CoP and corresponding time from peak anterior to peak posterior displacements of the CoP after sudden external perturbations and peak force during MVCs of the back and hamstring muscles in physiotherapists with non-specific back pain, in particular those with mild to moderate back pain. We will also investigate how the ability to produce maximum force in a short period of time during MVCs of the back and hamstring muscles relates to postural responses to externally induced perturbations in a control group without back pain.

## 2. Materials and Methods

### 2.1. Study Design

This cross-sectional study is designed to evaluate associations among measures of a perturbation-based balance test and back and hamstring strength tests in physiotherapists with non-specific back pain. The study will be implemented and reported in line with the Standard Protocol Items: Recommendations for Interventional Trials (SPIRIT) statement. The study design is illustrated in Figure 1.

### 2.3. Inclusion and Exclusion Criteria

Subjects will be screened for eligibility by the research team members. Those who report non-specific back pain [24,25] for more than 12 weeks [26,27,28,29] will be eligible. Inclusion criteria for LBP individuals and healthy controls will require no history of orthopedic or neurological conditions that could influence balance. Participants scoring ˂7 out of 10 on a numeric pain rating scale will be eligible for inclusion. Those who have previously undergone medically invasive procedures for back pain or have a diagnosis that may explain their low back symptoms (e.g., former injury or illness within the last 12 months) will be excluded. Exclusion criteria will also include pain not primarily generated from the musculoskeletal system, infections, diabetes, and pregnancy. As the strength of hamstring muscles will also be evaluated, participants who will report any other current muscular, joint, or neurological conditions affecting lower limb function will be excluded.

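### Eligibility requires back pain for more than 12 weeks with no upper limit, so the sample cannot support the Abstract's early-stage and pre-chronic claims

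*Protocol article*

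**What the plan says.** Section 2.3 (Inclusion and Exclusion Criteria) sets a minimum duration for the pain participants: "Those who report non-specific back pain [24,25] for more than 12 weeks [26,27,28,29] will be eligible". It states no maximum. The same section caps intensity: people scoring below 7 "out of 10 on a numeric pain rating scale will be eligible for inclusion". It also contains a 12-month window, but this belongs to the exclusion of people who "have a diagnosis that may explain their low back symptoms (e.g., former injury or illness within the last 12 months) will be excluded". It does not limit how long the pain itself may have lasted.

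The Abstract gives the study population as "physiotherapists with non-specific back pain in its early stages". It ends with the expectation that adding these tests would find back problems sooner, so that clinicians could "address them well before chronic back disorders occur". The Introduction argues for better variables and test conditions for the "assessment of healthcare workers with non-specific back pain in its early stages", and the Discussion uses the same early-stage phrase when it says where prediction efforts should go.

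**The concern.** The Abstract and the eligibility criterion describe different people. A reader of the Abstract expects physiotherapists near the onset of their back trouble. A reader of Section 2.3 sees that anyone in the first 12 weeks is not eligible, while someone with ten years of pain is, provided the score is below 7 and no other exclusion applies.

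At stake is the claim the results may carry. If the report keeps the Abstract's framing, associations found in people with persistent pain will be presented as evidence about early detection. Analysis cannot mend this afterwards, because nobody with pain of shorter duration will have been enrolled in the pain groups.

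**Working it through.** No formula applies and the article gives no figure to reproduce. The check compares every statement on duration, stage or chronicity with the criterion in Section 2.3.

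| Place | What it fixes | Does it limit duration from above? |
|---|---|---|
| Section 2.3, duration | More than 12 weeks of pain | No, it is a floor |
| Section 2.3, intensity | Score below 7 | No |
| Section 2.3, 12-month window | Explanatory injury or illness | No |
| Section 2.4, pain grades | Mild 1–3, moderate 4–6 | No |
| Section 2.4, last three months | Period referred to in describing moderate pain and its management | No |
| Section 2.13, pain model | Intensity and duration named as features of back pain | No, it does not restrict the sample |
| Abstract, Introduction, Discussion | Early-stage wording | Not defined |

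**Step 1: the eligible range.** Writing D for pain duration, the criteria give D > 12 weeks with no upper bound. A sample that is early by duration would need D ≤ c for some ceiling c. If c is 12 weeks or less, the two sets do not overlap. If c is more than 12 weeks, they overlap only between 12 weeks and c, and nothing in Section 2.3 keeps out people with D > c. For no choice of c does the criterion select an early-stage sample.

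**Step 2: can intensity stand in for stage?** The article nowhere says that early means mild or moderate. Section 2.13 names intensity and duration side by side as separate features. A person with years of pain scored 1–3 satisfies both the intensity cap and the duration floor, so low intensity does not bound duration.

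**Step 3: which statements describe this sample?** Only the Abstract attaches the early-stage label directly to the study's participants. The aim at the end of the Introduction, the design in Section 2.1, the analysis in Section 2.13 and the description of participants in the Discussion speak of non-specific or mild-to-moderate pain. These agree with Section 2.3. The other early-stage mentions in the Introduction and Discussion are rationale.

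**Step 4: does it touch the numbers?** The sample size is 34 per group plus 20%: 34 × 1.20 = 40.8, rounded up to 41. Two pain groups give 2 × 41 = 82. Pain duration does not enter this arithmetic, so the figures are unaffected.

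**The case against.** Four arguments can be made for the plan.

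- **The conflict sits mainly in the Abstract.** The formal aim, design and analysis fit Section 2.3, and the Introduction and Discussion use the early-stage phrase for a general need. This stands, and it makes the point one of wording and claim. It does not remove it, since the Abstract states the aim and is the part most readers see.
- **Neither early stages nor chronic is defined.** Early might mean low severity, which would fit the intensity cap and the exclusion of invasive procedures. A reader might infer that the trial enrols only chronic pain and so contradicts itself by definition. The document does not support that reading: equating more than 12 weeks with chronic relies on a convention that the article does not state. The point above does not need that label, and the severity reading is nowhere written down.
- **The planned inference is a cross-sectional correlation, and earlier detection is introduced only as an assumption.** This stands. A reader might infer that the 12-week floor biases or invalidates the correlations. It does not; they remain valid for the people enrolled. A cross-sectional correlation would not by itself show earlier detection at any duration, which is a further reason to soften the sentence.
- **The Discussion ties prevention partly to the pain-free controls.** That is correct, but people without back pain cannot represent back pain at an early stage, and the Abstract attaches that label to those with pain.

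It is also fair to say that putting the effect as 0% of the 82 pain participants having pain of 12 weeks or less only restates the criterion. It is not a measure of harm.

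**Conclusion.** The inconsistency is real but limited. Under any duration-based meaning of early, the sample defined in Section 2.3 cannot represent the population named in the Abstract, and limiting intensity does not change that. The results will apply to physiotherapists with mild-to-moderate non-specific back pain lasting more than 12 weeks. They will not support a statement about early-stage pain or about acting before chronic disorder.

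The effect is on the scope of the conclusion, not on any number in the plan. This rests on one assumption, that stage is read as elapsed time. If the authors mean severity, the text needs to say so, and the pre-chronic sentence would still need support that a sample with no upper limit on duration cannot give. This calls for correction before recruitment; it is not a flaw that undermines the study.

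**What to change.** Reconcile Section 2.3 with the Abstract, and bring the early-stage wording in the Introduction and Discussion into line. There are two ways.

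1. **Change the criterion.** Make the duration requirement in Section 2.3 match a stated definition of early stages. This changes who is recruited and may affect feasibility. The article leaves the timetable open (Section 2.2), so the change may still be possible.
2. **Change the claim.** Keep the criterion, describe the population and conclusion as mild-to-moderate non-specific back pain lasting more than 12 weeks, and remove the early-stage and pre-chronic claims for this sample. Early detection can remain as motivation for later work. The cost is rewording and a narrower claim; design, sample size, outcomes and analysis stay as they are.

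Showing the main balance–strength association by pain duration would help readers judge how far it carries, and the pain model in Section 2.13 already needs duration. It is an optional addition that the inconsistency does not require.

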### 2.4. Allocation

Participants will be divided into two groups according to the Numeric Rating Scale (mean of three assessments: current LBP, the usual/mean LBP within the last two weeks, and the worst LBP within the last two weeks), which is widely used in medical settings to obtain information about the level of a patient’s pain. The scale ranges from 0 (no pain at all) to 10 (unbearable pain). Participants experiencing mild pain (pain score 1–3), which is easy to manage physically as well as psychologically and does not interfere with most daily activities, and moderate pain (pain score 4–6), which interferes with daily activities and requires changes to manage pain symptoms during the last three months, will be considered. A control group of matched age, gender, and sample size will include those reporting no back pain.

### 2.5. Sample Size Estimation

The statistical power was calculated using the software program G*power 3.1 for Mac OS X. The calculation of the sample size was conducted with α = 0.05 (5% change of type I error) and 1 − β = 0.80 (power 80%) and using the results from our previous measurements. This indicated that a sample size of 34 individuals per group is needed to identify significant interaction effects. To reach this target sample size and achieve sufficient participant enrolment, 20% will be added to allow for dropouts.

### 2.6. Procedures

Participants will be asked to avoid exercises of higher intensity prior to the investigation. Before assessment, they will be given information on each testing protocol and the instructions during measurements. To eliminate learning effects, they will be required to practice a whole procedure beforehand. Tests will be conducted by the same examiners at the same time of the day for all participants. In comparison with frequently used laboratory tests, the use of portable and user-friendly diagnostic systems suited for testing in field conditions will be preferred in the present study. Using easy to administer tests that can reveal in a relatively short time period the impairment of postural and core stability and reduction in strength of particular muscle groups in LBP individuals could increase their applications in practice.

### 2.7. Data Collection and Management

The study will comprise the collection of personal demographic and outcome data. The questionnaire data will be transferred to a database and checked for correctness by research team members to ensure their quality. All information and outcome data will be stored in password-protected computers, which will be accessible by authorized research team members. Data management during the project and after the project’s completion will provide information on how data will be collected, documented, stored, and archived.

### 2.8. Descriptive Measures

Upon arrival at the laboratory, the participants’ characteristics will be summarized. These will include age, height, body mass, body composition, gender, and additional information related to back problems such as the amount of daily practice with clients, the type and duration of sporting activities, previous injuries, diseases, and so forth.

### 2.9. Primary Outcomes

#### Oswestry Disability Index

Participants will complete the Oswestry Low Back Pain Disability Questionnaire, which gives a subjective score of the level of function and/or disability in daily activities [30]. It is considered the ‘gold standard’ of low back functional outcome tools [30]. The Oswestry Disability Questionnaire data are reliable and have a scale of adequate width to reliably reveal worsening or improvement in most subjects [31]. The questionnaire consists of two parts—Oswestry Disability Index (ODI) version 2 and Visual Analogue Scale (VAS). The ODI questionnaire is designed to give information about how back or leg pain affects a patient’s ability to manage in everyday life. The ODI consists of 10 questions with a single choice of 6 answers. The VAS is a measurement instrument to measure the strength of pain experienced by a patient. Using a ruler, the score is determined by measuring the distance (mm) on a 10 cm line between ‘no pain at all’ and ‘my pain is as bad as it could be’. The patient marks a score from 0–10. A higher score indicates greater pain intensity. The pain VAS is a unidimensional measure of pain intensity, widely used in diverse adult populations. The combination of ODI and VAS is accepted worldwide and used in clinical practice because it is easy to use among patients and physicians.

### 2.10. Secondary Outcomes

#### 2.10.1. Postural Responses to Unexpected Perturbations

Participants will perform a perturbation-based balance test. They will be instructed to perform the test under two conditions: (1) bipedal and (2) tandem stance. Participants’ eyes will be focused on a spot on the wall at their eye level. They will be asked to stand barefoot on a force plate, a shoulder width apart, while their arms will be held in front horizontally. They will be asked to hold a bar with a 2 kg fixed load in their hands. After the test initiation, a signal from the computer will trigger a random load release over a 5 s period, therefore the participant will receive no cues as to when the perturbation will occur. The load release will produce a sudden change in the external forces acting on the participant that will lead to a slight anterior and a greater posterior CoP displacement. This postural perturbation will cause only a sway response, so the participant will not need to perform a step to maintain balance. The perturbation will be determined by peak anterior and peak posterior displacements within 1 s following the load drop. The recording will end 2–3 s following the load drop.

Three trials of each test condition will be randomly performed. The primary outcome measures will include peak anterior to peak posterior displacement of the CoP and the time from peak anterior to peak posterior displacement of the CoP. Secondary measures will include peak anterior displacement of the CoP, peak posterior displacement of the CoP, the time to peak anterior displacement of the CoP, and the time to peak posterior displacement of the CoP. These variables will be monitored by means of the FiTRO Sway Check (FiTRONiC, SVK). This system registers the actual force in the corners of the force plate and calculates an instant CoP position (sampling rate of 100 Hz, 12 bit AD signal conversion, resolution of the CoP position less than 0.1 mm, measuring range of 0–1000 N/s, non-linearity of +/−0.02% FS, combined error of 0.03%, sensitivity of 2 mV/V +/− 0.25%, overload capacity of 150%/sensor). Additionally, a ratio of the CoP anterior to the CoP posterior values will be estimated. The reliability of parameters of the perturbation-based balance test is good to excellent, with low SEM (7.1–10.7%) and high ICC values (0.78–0.92) [16]. This test is also sensitive in discriminating between sedentary and physically active young and early to late middle-aged adults. Good discriminatory accuracy of these variables is indicated by an area under the ROC curve >0.80 [14].

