### 2.13. Statistical Analysis

Statistical analysis of the data obtained will be conducted using the SPSS program for Windows, version 24.0 (SPSS, Inc., Chicago, IL, USA). The normality hypothesis will be tested using the Kolmogorov–Smirnov test. A parametric analysis will be conducted if the data are normally distributed. Associations between variables of the perturbation-based balance test and maximal isometric back and hamstring muscle strength in participants with mild to moderate back pain will be assessed using Pearson’s product moment correlation coefficient (small: r = 0.10–<0.30, medium: r = 0.30–<0.50, large: r = ≥ 0.50) [34]. Similarly, the correlation between RFD produced during MVCs of the back and hamstring muscles and postural responses to externally induced perturbations in the control group will be determined. A standard multiple regression analysis will be performed to investigate which of these variables of the muscle strength could be significant predictors of compensatory postural responses to unpredictable stimuli in individuals without back pain. The amount of variance explained will be determined by the coefficient of determination (r^2^). A multivariable logistic regression model will be used to determine associations of back pain (intensity and duration) with the covariates (age, gender, body mass, and eventually psychological factors and/or medical history of participants). The significance level will be set at α = 5%. Data will be presented as the mean (standard deviation).

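### The declared primary outcome (Oswestry) matches neither the study question nor the planned tests, and the centre-of-pressure (CoP) measures that do match are labelled both secondary and primary, so no test is identified as carrying the 5% level.

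*Protocol article*

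**What the plan says.** **Primary outcome by heading.** Under the heading "2.9. Primary Outcomes" the protocol article places one instrument: "Participants will complete the Oswestry Low Back Pain Disability Questionnaire". It describes two parts, the ODI and a visual analogue scale (VAS) for pain.

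**CoP measures.** The balance and strength tests stand under "2.10. Secondary Outcomes". Within that section, 2.10.1 states: "The primary outcome measures will include peak anterior to peak posterior displacement of the CoP", together with the time between those two peaks. It then continues: "Secondary measures will include peak anterior displacement of the CoP, peak posterior displacement of the CoP, the time to peak anterior displacement of the CoP", adds a fourth secondary variable (time to the posterior peak), and ends with: "Additionally, a ratio of the CoP anterior to the CoP posterior values will be estimated".

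**Aim.** The Abstract and the last paragraph of the Introduction state the study question as the relation of two CoP measures, peak-to-peak displacement and the time between the peaks, to peak force of the back and hamstring muscles in physiotherapists with back pain.

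**Analysis.** Section 2.13 plans four things:
- Pearson correlations of balance variables with back and hamstring strength in the back-pain group
- correlations of rate of force development (RFD) with postural responses in controls
- a multiple regression in people without back pain
- a logistic model of back pain intensity and duration on covariates.

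The error rate is given once, for everything: "The significance level will be set at α = 5" per cent.

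**The concern.** A primary outcome is meant to tell the reader which result answers the study's question and which test the error rate protects. Here the heading points to a disability score and the text of a secondary section points to two CoP measures. The analysis section follows the CoP measures without ranking any of its tests. Followed literally, the declared primary outcome gets no inferential test and the real question is reported as secondary.

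The Discussion says the relationship found will help to design a test battery for this workforce. If the primary tier is not settled before the data are seen, a chance association among several correlations could be given the weight of the main result.

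**Working it through.** **1. Match each candidate primary outcome to the aim and the analysis.**

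| Outcome | Label | In the stated aim? | Named in a section 2.13 inferential analysis? |
|---|---|---|---|
| ODI score | Primary (2.9) | No | No |
| Pain VAS (same questionnaire) | Primary (2.9) | No | Not by name; could be the intensity variable in the logistic model |
| Peak-to-peak CoP displacement; time between peaks | Secondary by heading, primary by text (2.10) | Yes | Yes, as balance-test variables |
| Four other CoP variables | Secondary (2.10.1) | No | Yes, as balance-test variables |

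No row is consistent with both the study question and a single primary label.

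**2. Does the sample size settle it?** The enrolment figures reproduce: 34 × 1.2 = 40.8, rounded up to 41 controls, and 2 × 41 = 82 with pain. The 34 itself cannot be reproduced, because section 2.5 gives no outcome and no effect size and refers only to interaction effects. It therefore does not show which outcome is primary.

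**3. Count the primary-tier tests if the two CoP measures are primary.** Inputs are 2 CoP measures (2.10.1), 2 stances (2.10.1), and back force plus hamstring force (2.10.2). Section 2.10.2 records left and right legs but does not say whether they are analysed separately.
- Legs combined: 2 × 2 × 2 = 8
- Legs separate: 2 × 2 × 3 = 12

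The article states neither count.

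**4. Chance of at least one false positive, each test at an unadjusted two-sided 5% (sidedness assumed).** If the tests are independent, this is 1 − 0.95^m:
- m = 8: 1 − 0.95^8 = 0.337, with 8 × 0.05 = 0.4 false positives expected
- m = 12: 1 − 0.95^12 = 0.460, with 12 × 0.05 = 0.6 expected

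The measures will be correlated, and the article does not give those correlations. A null simulation with n = 82 and equal correlation within each set (20,000 runs per setting) gives:

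| Assumed correlation among CoP measures / among forces | 8 tests | 12 tests |
|---|---|---|
| 0.3 / 0.5 | 29% | 39% |
| 0.5 / 0.7 | 25% | 32% |
| 0.7 / 0.9 | 18% | 21% |

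The range is roughly 20% to 40%.

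**5. What a clear rule would cost in power.** By the Fisher transformation, the correlation detectable with 80% power is r = tanh[(z(1−α/2) + 0.842)/√(n − 3)]. With n = 82, √79 = 8.888:
- one test at 0.05: tanh[(1.960 + 0.842)/8.888] = 0.305
- strictest of 8 (0.05/8 = 0.00625): tanh[(2.734 + 0.842)/8.888] = 0.382
- strictest of 12 (0.05/12 = 0.0042): tanh[(2.865 + 0.842)/8.888] = 0.394

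With 2 × 34 = 68 evaluable, the one-test and 12-test values become 0.334 and 0.430.

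**The case against.** **The labels may be less contradictory than they look.** Section 2.10.1 may be ranking variables within the balance test only, two main and four supporting. The two main ones are those in the aim, so a careful reader can tell what the study is about. This stands in part and lowers the severity. But the text does not say the ranking is local to that test, and the section headed primary still holds a different instrument.

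**A reader might infer that the ODI cannot be reported at all.** The article does not support that. Section 2.13 says data will be presented as mean and standard deviation, so a descriptive result is possible. The VAS part might also supply back pain intensity in the logistic model, although the text does not say so and section 2.4 offers a numeric rating scale as another source. What holds is narrower: no inferential analysis names the ODI score.

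**A reader might also count every CoP variable.** Seven variables × 2 stances × 3 forces = 42 correlations, and 1 − 0.95^42 = 0.88. That does not describe competing primary tests, because four variables are expressly secondary and the ratio is an addition. Nor can independence hold. Peak-to-peak displacement and the ratio are built from the same two peaks, and the time between peaks is the difference of the two times to peak.

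**Multiplicity rules often sit in an analysis plan, and this is a cross-sectional association study.** Both are fair. The absence of an adjustment rule is not in itself the defect. The defect is that the primary designation, on which any such rule depends, is inconsistent in the published text.

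**Conclusion.** The point holds as an inconsistency in designation. The outcome declared primary is not the study question and is named in no inferential analysis. The measures that are the study question carry both labels. No test is identified as carrying the 5% level.

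If the two CoP measures are taken as primary, 8 to 12 correlations share that tier. The chance of at least one false positive is then about 20% to 40%, or 34% to 46% under independence, against a nominal 5%. These figures rest on assumptions: both stances are analysed, tests are two-sided, there is one back-pain group of 82, and the correlations between measures are as shown above. They indicate the scale of the problem and are not properties stated in the plan.

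This should be fixed. It does not undermine the study, because the aim already shows which measures matter.

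**What to change.** - **Sections 2.9, 2.10 and 2.13:** designate peak-to-peak CoP displacement and the corresponding time, each against back and hamstring peak force in the back-pain group, as the primary analysis. Use that label throughout, and say whether the legs are combined or separate.
- **ODI:** move it to secondary or descriptive status and state how it is used, including whether its VAS or the numeric rating scale supplies pain intensity in the logistic model.
- **Error rate, before data are seen:** either name one correlation as the primary test at 5%, or share the 5% across the primary-tier correlations, for example by Holm. The choice of stance and muscle group is the sponsor's, since the aim gives no preference.
- **Everything else:** report the remaining CoP variables and the control-group RFD correlations as exploratory estimates with confidence intervals.

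The cost is rewording three sections, with no new data or participants. Fewer results can be called significant. With 82 participants the detectable correlation stays at about 0.305 for one named test and rises to about 0.39 at the strictest step of 12.
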